### 6.2 Preparation and labelling of Non Investigational Medicinal Product

Tc-99m-Nanocolloid-ICG is prepared by addition of 50 µl reconstituted ICG solution to a regularly labelled Tc-99m-Nanocoll solution. This exact solution is used in regular clinic practice for the sentinel node procedure in head-and-neck melanoma and oral carcinoma. We refer to the SmPC of Nanocoll and the SmPC of ICG.[21, 22].

## 7. METHODS

### 7.1 Study parameters/endpoints

#### 7.1.1 Main study parameter/endpoint

The primary endpoint of this study will be successful and tolerable (for the patient) identification of sentinel nodes on lymphoscintigraphy and SPECT imaging. The procedure will be considered successful and feasible when one or more sentinel nodes can be identified and localized in at least 7 out of the 10 patients. This qualitative endpoint will be assessed by consensus between the nuclear medicine physician ([name]), head and neck surgeons ([name], [name]) and radiation oncologists ([name], [name]).

#### 7.1.2 Secondary study parameters/endpoints (if applicable)

The secondary outcomes of this study will be the incidence of adverse events, pain score and analgesic use during and after peritumoral tracer injection, sentinel node yield in biopsy and occurrence of surgical complications after sentinel node biopsy. Adverse events will be scored according to CTCAE 4.0 criteria. Pain will be scored on a 1-10 visual-analogue scale immediately following tracer injection and 5, 10 and 120 minutes after injection. Sentinel node yield will be considered positive if at least one sentinel node can be investigated histopathologically. Finally, surgical complications will be scored according to standard complication registrations forms.

#### 7.1.3 Other study parameters (if applicable)

Patient demographics (age, sex, WHO performance score, smoking status) will be recorded. Furthermore, diagnostic results and baseline tumor characteristics will be registered for all patients. This will include stage, differentiation grade, tumor diameter, tumor volume and tumor epicentre location.

### 7.2 Study procedures

#### Nanocolloid injection and SPECT imaging procedures

- Patients will undergo all usual routine diagnostic procedures followed by review in the RCHNO multidisciplinary tumor board. Subsequently, patients will have a follow-up appointment to discuss diagnostic findings and the treatment proposal with their attending physician.
- After this appointment, patients will be informed about the sentinel node procedure and this study by one of the investigators and will be given at least 48 hours for consideration.
- If informed consent is given, patients will be scheduled for tracer injection at the department of nuclear medicine.
  - Sentinel node imaging will be scheduled the day before combined brachytherapy catheter implantation and SNB surgery. It is assured investigational procedures will not delay the start of usual treatment. See also: sentinel node biopsy procedures.

- Subcutaneous nanocolloid injection will be performed by the nuclear medicine physician with HNC sentinel node experience ([name]), if necessary consulting the brachytherapy radiation oncologist ([name] or [name]) or head and neck surgeon ([name] or [name]).
- The injection procedure will be performed according to the existing HNC sentinel node guidelines as follows [23][24]:
  - Patients will be positioned on a bed in a comfortable position. Local anesthesia will be administered and up to 4 peritumoral subcutaneous injections of 20MBq Tc-99m albumin colloid (Nanocoll)-ICG will be given. After injection, the injection location will be dabbed with gauze to remove excess fluid. Gentle pressure with gauze will be applied in case of minor hemorrhage. The anticipated duration of this injection procedure is 1-2 minutes.
- Ten minutes post-injection, static and dynamic scintigraphic imaging will be performed. These images will be taken from anterior and both lateral (left and right) positions. During this, patients will be positioned with the head in light extension using neck support.
- After two to four hours, static imaging from aforementioned positions will be repeated, followed by SPECT of the head-and-neck region.
- All SPECT images will be qualitatively assessed by an experienced HNC nuclear medicine physician ([name]) in consultation with the brachytherapy radiation oncologist ([name], [name]) and head-and-neck surgeon ([name], [name]).
  - Sentinel node locations will be also marked on the skin using a gamma probe. Ten second sentinel node emission registered by the gamma probe (so-called count) will be noted. This will be performed by the nuclear medicine physician.
- Either before or after sentinel node localization, patients will be hospitalized to undergo sentinel node biopsy the following day. This implies one additional day of hospitalization.
- The day following SPECT imaging, patients will undergo sentinel node biopsy (for more in depth information, see below), followed by the standard treatment consisting of implantation of brachytherapy catheters under general anaesthesia. Thereafter, they will be hospitalized for seven days the ENT ward. During this time brachytherapy is given two times daily for 14 fractions of 3.5 Gy. After the last fraction is administered, catheters are removed and patients are discharged either on the same or following day. The neck drains are removed if the wound fluid production is less than 10cc per 24 hours.

#### Sentinel node biopsy procedure

- An additional operating time of 2 hours will be scheduled to perform the sentinel node biopsy prior to brachytherapy catheter implantation.
- SNB will be performed prior to brachytherapy catheter implantation according to standard operating procedures in head-and-neck surgery. SNB will always be performed by an experienced head-and-neck surgeon and brachytherapy catheter implantation by a specialized brachytherapy radiation oncologist.
- The SNB will be performed according to the existing HNC sentinel node protocols as described under 5.1.

- After surgery, patients will be admitted at the ENT ward for seven days to undergo brachytherapy. This admission is a standard operating procedure for all NVC patients undergoing brachytherapy as described above.
  - Any harmonica drains left behind after SNB will be removed when drainage is below 10cc/24h; usually after 2 days. Transcutaneous stitches will be removed 7 days postoperatively (on the same day as brachytherapy catheter removal, usually one day before hospital discharge).
- Histopathological examination of the harvested lymph nodes will be performed following biopsy. The results will be reviewed in the RCHNO multidisciplinary tumor board. Eventual additional treatment will depend on this result, as explained below.
  - In case of fully tumor negative sentinel node(s), no additional treatment will be required. Additional staging information in form of N0(sn) will be noted and echo graphic follow-up of the neck shall be employed during follow-up.
  - In case of a positive sentinel node, additional completion neck node dissection will be advised within 3 weeks, according to existing head-and-neck SN guidelines [25].

As sentinel node positivity indicates regional disease extension, without treatment the patient has a high risk of relapse over the course of months, most likely with more extensive disease and possible extracapsular tumor extension. Direct neck dissection in case of positive sentinel node(s) will benefit affected patients. Rates of curation are higher when early elective surgery is employed, compared with therapeutic neck dissection in advanced regional disease [26]. A more comprehensive risk justification is provided in chapter 10.3 and will be discussed with patients prior to inclusion. Since complete neck dissection following tumor positive sentinel node biopsy is standard care and not subject of this research, it will not be explained in detail.

[figure not shown]

Figure 2: flowchart of procedures; solid line/white background = standard treatment, dashed/green background = investigational interventions.

### 7.3 Withdrawal of individual subjects

Subjects can leave the study at any time for any reason if they wish to do so without any consequences. The investigator can decide to withdraw a subject from the study for urgent medical reasons.

### 7.4 Replacement of individual subjects after withdrawal

After withdrawal of a subject, one additional subject will be recruited to achieve the aforementioned ten patient goal.

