### 7.5 Follow-up of subjects withdrawn from treatment

There will be no follow-up of subjects who withdraw from the study, unless the subject's withdrawal was a consequence of urgent medical reasons.

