### **8.3 Follow-up of adverse events**

All AEs will be followed until they have abated, or until a stable situation has been reached. Depending on the event, follow up may require additional tests or medical procedures as indicated, and/or referral to the general physician or a medical specialist. SAEs need to be reported till end of study within the Netherlands, as defined in the protocol.

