### **9.1 Primary study parameter**

The primary endpoint is successful localization of at least one sentinel node on SPECT imaging for each patient. This endpoint will be assessed by consensus between the nuclear medicine physician ([name]), head and neck surgeons ([name], [name]) and radiation oncologist ([name], [name]).

The procedure will be considered feasible when one or more sentinel nodes can be identified and localized in at least 7 out of the 10 patients. This cut-off takes in account a predicted learning curve, which can cause suboptimal results in the first few patients due to lack of experience in sentinel node imaging for this indication.

This qualitative endpoint will be presented in form of categorical data and also visualized as an anatomical map of sentinel node locations corresponding to primary tumor sites.

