## **12. Synthesis**

Potential issues of concern are not discussed because NANOCOLL Tc-99m-nanocolloid is a registered medical product. Furthermore, Tc-99m-nanocolloid-ICG is already routinely used, both in our clinic and worldwide, for sentinel node localization in melanoma, breast cancer and various head-and-neck malignancies such as high risk squamous cell carcinoma of the skin and cancer of the oral cavity [19, 33, 34].

Previously reported adverse effects of this agent have only been mild transient urticarial skin reactions, which in both described cases were easily managed by use of topical corticosteroids [28, 29]. Current consensus concludes that adverse effect are very rare, but nonetheless precautions have to be taken to anticipate upon a possible anaphylactic reaction[22] [21]. For this study, close monitoring of patients during and after nanocolloid administration will be assured. Furthermore, only patients with an acceptable WHO performance score of 0-2 will be included. In case of any signs of adverse reactions, tracer administration will be stopped and appropriate treatment steps will be set in motion in accordance with institution-wide allergic reaction protocols. Concluding, the estimated risk of subcutaneous nanocolloid-ICG injection is low, but adequate preventive measures in form of subject supervision and exclusion of patients in poor condition will be employed nevertheless.

Patients in this feasibility study might benefit from the results of the investigational procedure, whereas a tumor-positive sentinel node will prompt an early curative neck dissection, which may improve disease-free survival.

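### Section 7.4 lets a patient who starts the procedure and then withdraws be exchanged for a new one in the 7-of-10 count, which can raise the localisation rate

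*Protocol*

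**What the plan says.** - **Withdrawal (Protocol 7.3).** "Subjects can leave the study at any time for any reason if they wish to do so without any consequences". The investigator may also withdraw a subject for urgent medical reasons.
- **Replacement (7.4).** "After withdrawal of a subject, one additional subject will be recruited to achieve the aforementioned ten patient goal". The text does not separate withdrawal before injection from withdrawal after it, or one reason from another.
- **Decision rule (9.1; also the Summary, 4.4 and 7.1.1).** The procedure is feasible if "one or more sentinel nodes can be identified and localized in at least 7 out of the 10 patients".
- **Endpoint.** Section 7.1.1 asks for identification that the patient also tolerates. Section 9.1 asks only for localisation on SPECT.
- **Foreseen problems (section 2, research question 1).** Pain and being unable to inject the needed volume are named as possible site-specific difficulties.
- **Follow-up.** Section 7.5: "There will be no follow-up of subjects who withdraw from the study, unless the subject's withdrawal was a consequence of urgent medical reasons". Section 8.3: "All AEs will be followed until they have abated, or until a stable situation has been reached".

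**The concern.** The ten patients that 7.4 aims to reach are the ten in which the 7-of-10 rule is counted. Under 7.2, SPECT comes two to four hours after injection, so a patient can receive tracer and leave before the primary endpoint exists. If that patient left because the injection could not be tolerated or completed, this is the kind of problem the study sets out to find. Section 7.4 then brings in a new patient with a fresh chance of success, and no section keeps the first patient among the ten.

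This count is the study's only decision rule, and sections 1 and 10.3 make a larger multicentre study depend on its result. Section 9.1 already sets the cut-off low enough to allow for a learning curve, so replacing failures would add a second allowance that is not stated.

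**Working it through.** **1. The plan's own figure.** The rule is at least 7 of 10. Sections 4.4 and 9 state that no power calculation was done, and no null or target rate is given, so there is no calculation to reproduce. The rule's exact binomial behaviour, P(X ≥ 7 | n = 10, p), is 0.172 at p = 0.5, 0.382 at 0.6, 0.650 at 0.7, 0.879 at 0.8 and 0.987 at 0.9.

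**2. What the count hides, with no withdrawal rate assumed.** Suppose 7 patients are localised among the ten retained, and k further patients who started the procedure and failed were replaced. The rate among all who started is 7/(10 + k):

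- k = 1: 7/11 = 63.6%
- k = 2: 7/12 = 58.3%
- k = 3: 7/13 = 53.8%
- k = 4: 7/14 = 50.0%

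Under 7.4 each of these counts as 7/10 = 70% and meets the rule.

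One exchange can decide the verdict. With 6 successes and 4 failures the rule is not met. If one of the four withdraws and is replaced, it is met with probability p, the new patient's chance of success.

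**3. Effect on the chance of declaring feasibility (assumed inputs).** Let p be the true success rate and w the share of failures that withdraw and are replaced. The success rate among the ten retained is

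q = p / [p + (1 − p)(1 − w)].

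Example: p = 0.6, w = 0.25 gives q = 0.6 / (0.6 + 0.4 × 0.75) = 0.6/0.9 = 0.667. The chance of feasibility is then P(X ≥ 7 | 10, q).

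| True p | w = 0 | w = 10% | w = 25% | w = 50% |
|---|---|---|---|---|
| 0.5 | 0.172 | 0.218 | 0.313 | 0.559 |
| 0.6 | 0.382 | 0.447 | 0.559 | 0.776 |
| 0.7 | 0.650 | 0.706 | 0.791 | 0.917 |
| 0.8 | 0.879 | 0.906 | 0.941 | 0.982 |
| 0.9 | 0.987 | 0.991 | 0.995 | 0.999 |

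Both p and w are assumptions, since the protocol gives neither. The effect is largest where the true rate is mediocre and small where it is high.

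**4. Other directions.** If withdrawal is unrelated to outcome, q = p and there is no bias. If a share v of successes withdraws after imaging (say, before surgery) and is replaced, q = p(1 − v) / [p(1 − v) + 1 − p]. With p = 0.7 and v = 10%, q = 0.63/0.93 = 0.677, and the chance of feasibility falls from 0.650 to 0.589.

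**5. Sections 7.5 and 8.3 side by side.** Section 8.3 follows every adverse event until it has resolved or stabilised. Section 7.5 ends follow-up on withdrawal, except where the cause was urgent and medical. Both cannot hold for a patient who leaves by choice with an unresolved event that was not an urgent medical reason for leaving.

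**The case against.** The strongest reply is that the route to bias is narrow. Section 7.2 expects the injection to take one to two minutes under local anaesthesia, with SPECT the same day, and 10.3 expects the pain to pass and be tolerable. Few patients may leave in those hours. With 10% of failures replaced, the chance of feasibility moves only from 0.650 to 0.706 at p = 0.7. This stands, and it is why the larger shares in the table are illustrations only.

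It may also be said that 7.4 governs recruitment and leaves the analysis set to an SAP. This does not stand. Section 7.4 ties replacement to the goal of ten, and that ten is the denominator of the rule.

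A reader might infer more than the text supports:

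- **That failed scans drop out of the ten.** No section makes a failed scan a withdrawal. Such a patient has an observed primary outcome (not localised) and, under section 1, no biopsy follows.
- **That stopping the tracer is a withdrawal.** Section 12 says "In case of any signs of adverse reactions, tracer administration will be stopped". It does not say that the patient leaves the study.
- **That nobody who withdraws is followed.** Section 7.5 exempts withdrawal for urgent medical reasons.
- **That intolerance and complications are hidden.** Section 8.2.1 records all adverse events reported or observed, and nothing deletes data collected before withdrawal.

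**Conclusion.** The point holds as a conditional risk. The replacement rule allows a patient who started the procedure and failed to be exchanged within a fixed count of ten, and the localisation rate can then be too high. It would go too far to say that the primary result is biased upward. That needs withdrawal before the endpoint to be related to failure, and step 4 shows cases with no bias or a downward one.

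The size cannot be derived from the protocol. Step 2 is arithmetic that holds for any withdrawal rate, while step 3 rests wholly on assumed values of p and w. In a descriptive study of ten patients that leads to a larger one, this should be fixed, but it does not undermine the design. The conflict between 7.5 and 8.3 is a separate and smaller matter of wording.

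**What to change.** - **Section 7.4.** Replace only subjects who withdraw before the injection procedure is started. Keep every patient in whom injection is attempted in the primary denominator with the observed imaging result. Count those with no node localised as failures, including failed or stopped injection and withdrawal before imaging. Anchoring on the attempt, not on the first completed injection, keeps patients who cannot be injected in the count. A success already observed also stays, which removes the downward case.
- **Reporting.** List all withdrawals and replacements with timing and reason.
- **Sections 7.5 and 8.3.** Reconcile them for patients who withdraw, other than for urgent medical reasons, with an unresolved adverse event.

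One case stays open: a node is seen but the injection was not tolerated. Whether that is a success depends on 7.1.1 or 9.1, and those two definitions should be aligned.

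The cost is a few sentences and no new procedures. The rate may look less favourable, and the rule becomes stricter where patients leave before imaging for unrelated reasons. For example, if 10% of all injected patients did so at p = 0.7, the success rate would be 0.7 × 0.9 = 0.63 and the chance of feasibility 0.460, against 0.650 with replacement. Listing the reasons lets a reader judge such cases.

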### 7.5 Follow-up of subjects withdrawn from treatment

There will be no follow-up of subjects who withdraw from the study, unless the subject's withdrawal was a consequence of urgent medical reasons.

### 7.6 Premature termination of the study

The study and the clinical introduction of the sentinel node procedure will both be terminated prematurely when unexpected serious adverse events are experienced which may endanger other subjects. If the trial is prematurely terminated the investigator will promptly inform the trial subjects, the medical research ethics committee (METC) and competent authority. A

detailed written explanation of the termination will be provided. Appropriate follow-up and treatment of trial subjects will be ensured.

## 8. SAFETY REPORTING

### 8.1 Temporary halt for reasons of subject safety

In accordance to section 10, subsection 4, of the WMO, the sponsor will suspend the study if there is sufficient ground that continuation of the study will jeopardise subject health or safety. The sponsor will notify the accredited METC without undue delay of a temporary halt including the reason for such an action. The study will be suspended pending a further positive decision by the accredited METC. The investigator will take care that all subjects are kept informed.

### 8.2 AEs, SAEs and SUSARs

#### 8.2.1 Adverse events (AEs)

Adverse events are defined as any undesirable experience occurring to a subject during the study, whether or not considered related to the diagnostic interventions. All adverse events reported spontaneously by the subject or observed by the investigator or his staff will be recorded.

#### 8.2.2 Serious adverse events (SAEs)

A serious adverse event is any untoward medical occurrence or effect that

- results in death;
- is life threatening (at the time of the event);
- requires hospitalisation or prolongation of existing inpatients' hospitalisation;
- results in persistent or significant disability or incapacity;
- any other important medical event that did not result in any of the outcomes listed above due to medical or surgical intervention but could have been based upon appropriate judgement by the investigator.

The elective hospital admission including the aforementioned one planned additional hospitalization day will not be considered serious adverse events.

The investigator will report all SAEs to the sponsor without undue delay after obtaining knowledge of the events, except for the following SAE: prolongation of hospitalization due to brachytherapy related complications (specifically: treatment re-planning due to loss of an interstitial catheter and therefore prolongation of radiotherapeutic treatment). Prolongation of admission caused by surgical/sentinel node biopsy complications will be reported without delay.

The sponsor will report the SAEs through the web portal *ToetsingOnline* to the accredited METC that approved the protocol, within 7 days of first knowledge for SAEs that result in death or are life threatening followed by a period of maximum of 8 days to complete the initial preliminary report. All other SAEs will be reported within a period of maximum 15 days after the sponsor has first knowledge of the serious adverse events.

### **8.3 Follow-up of adverse events**

All AEs will be followed until they have abated, or until a stable situation has been reached. Depending on the event, follow up may require additional tests or medical procedures as indicated, and/or referral to the general physician or a medical specialist. SAEs need to be reported till end of study within the Netherlands, as defined in the protocol.

### **8.4 [Data Safety Monitoring Board (DSMB) / Safety Committee]**

Following EMEA guidelines on Data Monitoring Committees, a DSMB is not deemed beneficial and necessary for this study. Study procedures will be performed by the aforementioned team of experts, in a monitored clinical setting and with a priority for patient safety.

